# A prospective, multicenter, open-label, single-arm clinical trial design to evaluate the safety and efficacy of ^90^Y resin microspheres for the treatment of unresectable HCC: the DOORwaY90 (Duration Of Objective Response with arterial Ytrrium-90) study

**DOI:** 10.1186/s12876-022-02204-1

**Published:** 2022-03-28

**Keywords:** Radioembolization, SIRT, ^90^Y resin microspheres, Hepatocellular carcinoma (HCC)

## Abstract

**Background:**

Selective internal radiation therapy (SIRT) with yttrium-90 (^90^Y) resin microspheres is an established locoregional treatment option for unresectable hepatocellular carcinoma (HCC), which delivers a lethal dose of radiation to hepatic tumors, while sparing surrounding healthy tissue. DOORwaY90 is a prospective, multicenter, open-label, single arm study, designed to evaluate the safety and effectiveness of ^90^Y resin microspheres as first-line treatment in patients with unresectable/unablatable HCC. It is unique in that it is the first study with resin microspheres to utilize a personalized ^90^Y dosimetry approach, and independent review for treatment planning and response assessment.

**Methods:**

Eligibility criteria include unresectable/unablatable HCC, Barcelona Clinic Liver Cancer stage A, B1, B2, or C with a maximal single tumor diameter of ≤ 8 cm, and a sum of maximal tumor diameters of ≤ 12 cm, and at least one tumor ≥ 2 cm (long axis) per localized, modified Response Evaluation Criteria in Solid Tumors. Partition model dosimetry is used to determine the optimal dose; the target mean dose to tumor is ≥ 150 Gy. Patients are assessed at baseline and at regular intervals up until 12 months of treatment for response rates, safety, and quality of life (QoL). Post-treatment dosimetry is used to assess dose delivered to tumor and consider if retreatment is necessary. The co-primary endpoints are best objective response rate and duration of response. Secondary endpoints include grade ≥ 3 toxicity, QoL, and incidence of liver resection and transplantation post SIRT. Target recruitment is 100 patients.

**Discussion:**

The results of this trial should provide further information on the potential use of SIRT with ^90^Y resin microspheres as first-line therapy for unresectable HCC.

***Trial registration*:**

Clinicaltrials.gov; NCT04736121; date of 1st registration, January 27, 2021, https://clinicaltrials.gov/ct2/show/NCT04736121.

**Supplementary Information:**

The online version contains supplementary material available at 10.1186/s12876-022-02204-1.

## Background

Hepatocellular carcinoma (HCC) is the most common type of primary liver cancer, with the third highest solid tumor mortality rate after lung and colon cancer [1]. In the USA, it is estimated that in 2020, 42,810 new cases of HCC were diagnosed, with a 5-year survival rate of 18% [2]. In early-intermediate HCC, liver resection or liver transplantation may be appropriate treatment options [3], but approximately 70–80% of patients with HCC are not diagnosed early enough to benefit from these potentially curative treatments [4, 5].

Several treatment strategies are available for patients with unresectable HCC. One such strategy is selective internal radiation therapy (SIRT), also referred to as radioembolization. SIRT is a technique that selectively deposits yttrium-90 (^90^Y) microspheres into the hepatic vasculature to deliver a lethal dose of radiation to the tumor(s). Surrounding healthy liver tissue can be spared by selectively delivering the microspheres into specific Couinaud segment(s) or the tumor vasculature itself. SIRT exploits the tumor’s hypervascularity relative to healthy tissue, delivering safe levels of radiation to normal tissue while achieving a selective tumoricidal dose. Relative to bland embolization or chemoembolization, SIRT minimizes potential macroembolic effect. Instead, SIRT leads to partial occlusion (microembolization) of the vascular supply to the tumor while the beta-radiation emitted from ^90^Y induces DNA damage in tumor cells [6, 7].

SIRT has the potential to not only delay local progression but also to downstage the disease to allow resection or transplantation if the disease meets Milan, or similar, criteria [8–10]. Previous randomized clinical trials of first-line ^90^Y resin microspheres (SIR-Spheres®, Sirtex Medical) for advanced HCC did not meet their primary endpoints for a number of reasons that include: (1) inadequate dosimetry-treatment planning; (2) poorly controlled patient populations; and (3) no post-treatment confirmation of absorbed dose [11–13]. These trials were initiated and conducted before the development of our current understanding of radiation-dose–response following SIRT, and before the widespread acceptance of personalized dosimetry for SIRT [14].

To overcome the limitations of these trials, we initiated the Duration Of Objective Response with arterial Yttrium-90 (DOORwaY90) study of ^90^Y resin microspheres, which utilizes a personalized dosimetry approach using the partition model and is recruiting patients with unresectable HCC (Barcelona Clinic Liver Cancer [BCLC] stage A, B1, B2 and C). All eligible patients receive ^90^Y resin microspheres using either a selective or lobar approach.

## Methods/design

### Study design

The DOORwaY90 trial is a pivotal, prospective, multicenter, open-label, single-arm study. The objective is to evaluate the safety and effectiveness of ^90^Y resin microspheres as first-line treatment for unresectable HCC (BCLC stages A, B1, B2, and C).

All relevant institutional and local ethics committee approvals were gained before commencing the study (Additional file 1). The study is being conducted in 14 investigational sites in the USA and aims to enroll approximately 100 patients (Fig. 1). No single site will enroll more than 20% of the study population. Written informed consent is obtained from all participants (or their legally authorized representatives) prior to participation in this study.

**Fig. 1 Fig1:**
[figure not shown]
Study flow diagram

Investigators and study sites are required to permit study-related monitoring, audits, Institutional Review Board (IRB) review, and regulatory inspection(s) and provide direct access to source data/documents. This study will have oversight by a Data and Safety Monitoring Board (DSMB), which will review summarized safety data (including enrollment, protocol deviations, and adverse events) and will use stopping rules as defined in the DSMB Charter. The sponsor may also terminate or suspend the study if the DSMB stopping rules have been met. Sites must submit any protocol amendments to the IRB and are required to forward a copy of the written approval to the CRO. The final dataset will be available to the sponsor/CRO and IRB.

Important aspects of the trial include: (1) personalized dosimetry for treatment planning; (2) centralized review of the treatment plans and verification scans; (3) use of an independent core laboratory for response assessment; (4) a specific patient population that would benefit from locoregional treatment; (5) potentially curative treatment; (6) confirmation of absorbed dose delivered to the tumor; and (7) assessment of long-term toxicity.

### Patients

Adult (≥ 18 years of age) patients enrolled into this study have a diagnosis of HCC BCLC stage A, B1, B2, or C with a maximal single lesion size of ≤ 8 cm and a sum of maximal tumor diameters of ≤ 12 cm, with the entire tumor burden expected to be treatable within the perfused volume. Patients cannot be considered suitable for treatment by resection or ablation at the time of study entry. For safety considerations, ≥ 33% of the total liver volume (body surface area-based) must be disease free and not treated with ^90^Y [15]. All inclusion and exclusion criteria are summarized in Table 1.

**Table 1 Tab1:** Patient eligibility criteria for DOORwaY90 trial

Inclusion criteria	Exclusion criteria
Willing, able, and mentally competent to provide written informed consent Age 18 or older at the time of consent Diagnosis of HCC with Liver Imaging Reporting and Data System (LI-RADS) 4 or 5 or by histology Treatment-naïve patients, including no prior locoregional therapies in the liver and no systemic therapy for HCC BCLC stage A, B1, B2, and C with maximal single tumor size of ≤ 8 cm and sum of the maximal tumor dimensions of ≤ 12 cm, with the entire tumor burden expected to be treatable within the perfused volume All tumors must be measurable by CT or MRI according to localized mRECIST At least one lesion ≥ 2 cm in diameter (long axis) measured according to mRECIST criteria by CT or MRI Child Pugh score A5 or A6 at baseline Albumin-Bilirubin (ALBI) grade = 1 or 2 at baseline Eastern Cooperative Oncology Group (ECOG) performance score 0 or 1 at baseline Adequate blood count, liver enzymes, and renal function at baseline Platelet count > 50,000/µl (no platelet transfusion or growth factors) White blood cell count ≥ 3 × 10^9^/l Hemoglobin >8.5 g/dl AST and ALT <5 × upper limit normal Bilirubin ≤ 2.0 mg/dl Albumin >3.0 g/dl Creatinine <2.0 mg/dl INR ≤ 2.0 Glomerular filtration rate > 50 Negative serum pregnancy test at baseline Life expectancy of ≥ 6 months with life expectancy of > 3 months if receiving no active treatment	Patient eligible for ablation or resection for their malignancy in the opinion of the investigator at screening visit Prior systemic anti-cancer therapy (including immunotherapy and/or targeted therapy), radiotherapy or use of other investigational agents for the treatment of HCC Intrahepatic arteriovenous shunting. (arteriovenous shunting resulting from a biopsy is allowed but must be embolized during the pre-treatment mapping procedure) Incompetent biliary duct system, prior biliary intervention or a compromised Ampulla of Vater Planned localized cancer treatment to the liver, other than the study treatment, during the study Planned systemic cancer treatment during the study Portal vein thrombosis Extrahepatic disease Patients with contraindications to angiography and selective visceral catheterization Evidence of extrahepatic collateral supply to the tumor Evidence of potential delivery of mean radiation dose > 30 Gy to the lungs (single treatment) Evidence of any detectable ^99m^Tc-MAA flow to outside of the liver in the abdomen, after application of established angiographic techniques to stop or mitigate such flow (e.g., placing catheter distal to gastric vessels or coiling) Evidence that < 33% of the total liver volume is disease-free and will be spared ^90^Y resin microsphere treatment Prior liver resection and/or liver transplant Female patients who are pregnant, breastfeeding, or premenopausal and unwilling to use an effective method of contraception through the 1-year follow-up; males unwilling to use effective method of contraception for 30 days post-procedure Medical history of clotting disorders Underlying pulmonary disease requiring chronic oxygen therapy Evidence of portal hypertension with ascites as seen on cross-sectional imaging or history of variceal bleeding within 6 months before screening Concurrently enrolled in another study unless it is an observational, non-interventional study Active infection (hepatitis B (HBV) infection with ongoing HBV treatment and successfully treated hepatitis C infection is allowed) History of other cancer with current active treatment Patients with drug or alcohol dependency (within 6 months of study entry) in the opinion of the investigator History of severe allergy or intolerance to contrast agents, narcotics, or sedatives Any condition that, in the opinion of the investigator, would interfere with safe delivery of the study treatment or with the interpretation of study results

### Treatment

#### Pre-SIRT

The methods of catheter angiography and hepatic arterial mapping for SIRT are well established and reviewed elsewhere [16]. Briefly, angiography is performed to identify the appropriate catheter position for administration of the microspheres and to visualize any hepatic or gastrointestinal vessels that may result in non-target dose deposition. If found, these vessels must be successfully circumvented before proceeding with SIRT, either by adjusting the catheter placement or by performing prophylactic embolization. After this evaluation, technetium-99m (^99m^Tc)-macroaggregated albumin (MAA) is administered via the catheter at the planned treatment position as a surrogate for the ^90^Y microspheres. The biodistribution of the ^99m^Tc-MAA is assessed via planar scintigraphy of the chest and abdomen and single photon emission computed tomography/computed tomography (SPECT/CT) of the liver.

Target and non-target tumor compartments and the treated non-tumoral liver tissue compartments are segmented, and volumes and ^99m^Tc-MAA uptake determined. The patient-specific target tumor-to-normal ratio (TNR) that is needed as input for the partition model is then calculated. The catheter tip during ^99m^Tc-MAA injection would typically be placed at the same anatomical position from which ^90^Y resin microspheres will be administered. The exception is when segmental treatments are planned, in which case, lobar ^99m^Tc-MAA injection may be performed, at the discretion of the clinician. When a segmental treatment (number of segments ≤ 2) is planned, the TNR value is then set to 1.0 (i.e., plan as a single compartment), and the minimum planned dose to the segment is > 150 Gy. Multi-vessel treatments are permitted. However, a cone-beam computed tomography (CBCT) or in-room fan beam CT should be performed to adequately determine the perfused volume. ^99m^Tc-MAA is administered at each location; exceptions include segmentectomy cases. Clinical justification for adjustment or alteration of catheter position between sessions is documented. All pre-SIRT images and contours are assessed jointly by the treatment physician and the Eligibility Review Committee to confirm treatment planning dosimetry and approach based on the dosimetry principles and constraints outlined next.

#### Treatment plan dosimetry

CBCT or in-room fan beam CT is used for volume calculation. 3D volumetric software is used to segment the total liver volume (TLV), the volume of perfused normal liver parenchyma (NLp) and the treated tumor (TT) compartments in the liver, and to determine their volume (in ml) and the total ^99m^Tc-MAA counts in the NLp and TT compartments. Soft-tissue density of 1.06 g/ml is used to determine the mass (in kg) of the TT compartment (M_tumor_) and the mass of the perfused normal liver compartment (M_NLp_). The patient-specific tumor uptake ratio, R, is calculated (using MIM Maestro) as:R = tumor compartment (total ^99m^Tc-MAA counts/total volume of interest)/perfused normal liver compartment (total ^99m^Tc-MAA counts/total volume of interest)

Based on partition model equations [17], the administered activity (A_admin_) required to meet the intended mean dose to the tumor compartment, D_tumor_, is calculated according to the formula:A_admin_ [GBq] = D_tumor_ [Gy] × M_tumor_ [kg]/(49.7 [Gy-kg/GBq] × (1-LSF) × R × M_tumor_/(M_NLp_ + R × M_tumor_)), where LSF is the lung shunt fraction.

The mean dose to the perfused normal liver compartment, D_NLp_, is calculated as:D_NLp_ [Gy] = D_tumor_ [Gy]/R.

#### Lung dosimetry

Regions of interest are drawn around the lung region and the liver region in both the anterior and the posterior views of planar scintigraphy. The view with the highest ^99m^Tc-MAA counts for the liver region is used to determine the ^99m^Tc-MAA counts in the lung region and the ^99m^Tc-MAA counts in the liver region for the calculation of the lung shunt fraction (LSF). The LSF is calculated using the following formula:LSF = (counts in lung region)/((counts in lung region) + (counts in liver region))

The mean lung dose (D_lung_) corresponding to a specific LSF can be determined as:D_lung_ [Gy] = A_admin_ [GBq] × LSF × 49.7 [Gy-kg/GBq]/M_lung_ [kg], where M_lung_ is the mass of lung tissue [kg].

The M_lung_ can be calculated using a patient-specific CT scan or can be estimated as 1 kg.

#### Treatment plan dosimetry constraints

**Normal liver constraints:** patients are excluded if < 33% of the total liver volume based on body surface area (TLV^BSA^) is tumor free, and therefore, left untreated. The TLV^BSA^ is calculated based on the method of Vauthey et al. [15] as:TLV^BSA^ [ml] = − 794.4 + 1267.3 × (height [cm] × weight [kg]/3600)^0.5^

If the ^90^Y treatment-spared liver volume is ≥ 33% but < 40% of the TLV^BSA^, the dose to the perfused normal liver parenchyma will be limited to < 150 Gy [14]. If the ^90^Y treatment-spared liver volume is ≥ 40% of the TLV^BSA^, there will be no upper limit to the dose allowed to the perfused normal liver parenchyma [18].

**Lung mean dose (D**_**lung**_**) constraints**: D_lung_ ≤ 30 Gy for a single treatment, and the cumulative lung mean dose < 50 Gy if the patient is re-treated.

**Tumor mean dose (D**_**tumor**_**) constraints**: the planned mean dose to the tumor must be in the range of 150–400 Gy. The lower limit of 150 Gy was based on the estimated mean dose required to achieve a complete response (CR) in previous studies [19, 20]. In the unlikely event that the planned mean dose to the total tumor compartment cannot exceed 150 Gy, the patient is considered a screening failure.

#### SIRT procedure

All treatments are performed with 3-day FLEXdose delivery option in a single treatment session using a selective or lobar approach. To optimize the predictive value of the ^99m^Tc-MAA intra-hepatic distribution, the catheter tip during ^99m^Tc-MAA injection is recommended to be placed at the same anatomical position from which ^90^Y resin microspheres will be administered (a deviation greater than ± 0.5 cm is allowed, if necessary, but must be documented; likewise, the occurrence of stasis will be documented).

#### After the SIRT procedure

Post-treatment assessment is conducted by imaging of the patient’s abdomen with ^90^Y SPECT/CT or ^90^Y PET/CT. Post-SIRT images are assessed by the Eligibility Review Committee using FDA-approved software to qualitatively confirm tumor targeting, quantify the mean tumor dose delivered, and to decide if re-treatment may be necessary.

#### Repeat SIRT

If the mean tumor dose delivered, based on post-treatment ^90^Y SPECT/CT or ^90^Y PET/CT imaging, was estimated to be < 100 Gy, SIRT re-treatment may be performed at the discretion of the treating physician within 4 weeks of the index procedure.

### Assessments

Treated patients will be assessed at baseline (no more than 28 days before SIRT), and at 1, 2, 4, 6, 9 and 12 months (± 2 weeks) and at 24 months (± 1 month) after SIRT. All patients are assessed according to the schedule summarized in Table 2. All images used to assess tumor response are reviewed at an independent centralized laboratory (American College of Radiology Center for Research and Innovation, Philadelphia, PA; ACR). Patients may be withdrawn from the study due to loss of follow-up, death, withdrawal of consent, adverse events, investigator decision, or if there is failed SIRT implantation. If a patient withdraws from the study a study completion electronic case report form must be completed, describing the reason for discontinuation. After 24 months and exit from the study, patients will be assessed and managed as per usual care.

**Table 2 Tab2:** DOORwaY90 trial assessment schedule

Evaluations	Baseline^1^	Eligibility review committee approval	SIRT treatment	Re-treatment^2^	1 month (± 2 weeks)	Follow-up visits 2, 4, 6, 9 and 12 months (± 2 weeks) post-index procedure	2 years (± 1 month) clinic/phone
Patient informed consent	X						
Inclusion/exclusion assessment	X						
Physical exam including vital signs	X					X	
Demographics and medical history	X						
Pregnancy test	X						
Child–Pugh assessment	X			X			
Laboratory tests^3^	X		X	X	X	X	
^99m^Tc-MAA lung shunt scan and liver SPECT/CT	X						
Imaging (CT or MRI) of chest, abdomen, and pelvis	X					X^4^	
Hepatic angiography	X		X	X			
Treatment plan assessment	X						
ECOG performance test	X						
Medication assessment	X		X	X		X^5^	
Tumor response (mRECIST)^6^	X					X	
CBCT (or in-room fan-beam CT)	X		X	X			
^90^Y resin microsphere treatment			X	X			
Post-treatment imaging of abdomen with ^90^Y SPECT/CT or ^90^Y PET/CT			X	X			
Adverse event assessment	X		X	X	X	X	X
Quality of life questionnaires (EQ-5D-5L, FACT-Hep)			X^7^			X	

^1^Performed within 28 days prior to SIRT treatment procedure

^2^SIRT re-treatment may occur at the discretion of the treating physician within 4 weeks of index procedure

^3^CBC/Diff, biochemistry, total protein, AST, ALT, ALP, bilirubin, albumin, creatinine, prothrombin time, partial thromboplastin time, international normalized ratio. Hepatitis B and C, and serology at baseline visit only

^4^Modality of imaging (CT or MRI) must match method used at baseline

^5^Information on all concomitant medications collected for first 2 months; after 2 months, only oncologic and/or liver specific medications

^6^Images sent to core laboratory for analysis

^7^Completed pre-procedure

### Outcomes

The co-primary endpoints are localized objective response rate (ORR; CR or partial response [PR]) using modified Response Evaluation Criteria in Solid Tumors (mRECIST) [21] with best response through 9 months, and duration of response (DoR), defined as the time-interval from first achieving a response (i.e., CR or PR) until disease progression (≥ 6 months for ≥ 60% of responders).

Secondary endpoints include: grade ≥ 3 toxicity (Common Terminology Criteria for Adverse Events, CTCAE v5.0) at 3 months and 6 months; quality of life (QoL) measured by Functional Assessment of Cancer Therapy-Hepatobiliary (FACT-Hep) questionnaire and the five-level EuroQol five-dimensional questionnaire (EQ-5D-5L); liver resection rate; and liver transplant rate.

### Sample size calculation and statistical considerations

Continuous data will be summarized using descriptive statistics: sample size, mean, standard deviation, standard error, median, and range or interquartile range. Discrete variables will be summarized using frequency counts and percentages. All statistical analyses will be performed using SAS (version 9.4 or higher, SAS Institute Inc. Cary, NC), R (version 3.2 or higher, R Foundation for Statistical Computing, Vienna, Austria) or other widely accepted statistical or graphical software.

Primary analyses will be conducted under the principles of intent-to-treat (ITT), using the full analysis set (FAS) as defined in ICH E9 (Statistical Principles for Clinical Trials). Additionally, a per-protocol (PP) population is defined, including ITT patients who met all inclusion and exclusion criteria, received the intended dose of 150–400 Gy, and had no major protocol violations.

Methods for replacing missing data such as last value carried forward or multiple imputation will not be routinely used for the primary study analyses. For the purposes of defining the primary endpoints, death before the first attempt at evaluation will be defined as failure of the endpoint in question, and if no evaluable mRECIST data are collected for a patient, they will be classified as a failure for the ORR endpoint and as missing data for the DoR endpoint. Planned subgroup analyses will be conducted to evaluate consistency of results by gender and dosimetry method. Additionally, a dose–response analysis will be conducted to estimate the threshold mean tumor dose for response for tumors ≥ 3 cm. For the co-primary endpoint ORR, all lesions in the treated portion of the liver will be included for analysis, with up to 2 lesions per patient defined as target lesions and the rest non-target lesions. ORR results will be presented as the proportion of successes (CR or PR) with corresponding confidence limits calculated by the exact binomial (Clopper-Pearson) method. The performance goal is a lower confidence interval for best response on ORR of 40%. A DoR of ≥ 6 months in ≥ 60% of responding patients is the goal of the co-primary endpoint.

An overall summary of adverse events (AEs) will be presented, which will include the number and percentage of patients with at least one AE, and the total number of AEs. All AEs will be adjudicated by a Clinical Events Committee (CEC). AEs will additionally be classified according to the Medical Dictionary for Regulatory Activities (MedDRA) dictionary, summarized by severity, relationship to SIRT, outcome and seriousness. Serious adverse events (SAEs) will be summarized according to severity and relationship. Multiple occurrences of the same AE are counted once at the maximum grade and strongest relationship, as appropriate.

The postulated success rate for the ORR primary endpoint is estimated to be 55–60% based on previous experience with the study device and expert opinion on its effectiveness in the target population; as stated, the performance goal applied to the lower confidence bound for this estimate is 40%. Given a two-sided test at an alpha of 0.05 and desired power of 80%, the required evaluable sample size using the exact method for a single proportion and the worst estimate above is no greater than 90. Therefore, a study sample size of 100 is targeted to provide adequate powering for hypothesis testing as described above. Consent from up to 150 patients is anticipated to achieve the sample size of 100 patients, based on previous experience of eligibility failure of 33%. The overall study duration, from screening the first patient to the final follow-up visit, data analysis and final report, is expected to be approximately 39 months.

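### Duration of response ends only at progression, so a responder who dies progression-free has no event, and the 60% co-primary goal is tilted upward

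*Protocol article*

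**What the plan says.** Three statements in the protocol article bear on this point.

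- **Definition (Outcomes).** DoR is "defined as the time-interval from first achieving a response (i.e., CR or PR) until disease progression". No other end event is named.
- **Goal (Sample size calculation and statistical considerations).** "A DoR of ≥ 6 months in ≥ 60% of responding patients is the goal of the co-primary endpoint". No confidence bound or test is attached to it. The Outcomes section gives the same 60% figure, also in responders.
- **Deaths and missing data (same section).** For the primary endpoints, in the plural, "death before the first attempt at evaluation will be defined as failure of the endpoint in question". The sentence goes on to say that patients with no evaluable mRECIST data are "classified as a failure for the ORR endpoint and as missing data for the DoR endpoint". Replacement of missing data "will not be routinely used for the primary study analyses".

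Elsewhere, the Assessments section lists death among the reasons for withdrawal and attaches no endpoint consequence to it.

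**The concern.** **Main point.** The article makes an explicit rule about death for the primary endpoints, but the rule covers only deaths before the first evaluation. For DoR the deaths that matter are those after a response. Such a patient cannot fall under the printed rule and does not meet the printed end event. Whether the patient is then counted as never having progressed, censored or left out, the death is not a failure of durability. Compared with a measure in which death ends the response, each of these treatments gives a higher proportion.

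The trial is single-arm and pivotal, so there is no control group in which the same effect would occur. The DoR goal is a bare proportion, so a few patients can decide whether a co-primary endpoint is met.

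**Secondary point.** The sentence on early deaths gives one patient two DoR statuses. Someone who dies before any scan is a failure under its first clause. The same person has no evaluable mRECIST data and is therefore missing under its second clause.

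**Working it through.** **1. The plan's own figure.** The only sample-size figure is for ORR: no more than 90 evaluable patients, from a 40% goal, a 55% worst-case rate, two-sided alpha 0.05 and 80% power. The exact binomial test reproduces it. At n = 90, rejecting at 46 or more responses gives P(X ≥ 46 | 0.40) = 0.0213, below 0.025, and P(X ≥ 46 | 0.55) = 80.2%. This calculation does not involve DoR. The article gives no power or sample size for DoR, so there is none to reproduce.

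**2. Inputs for DoR.**
- Responders: 55% to 60% of 100 patients, hence 55 to 60 (postulated ORR and target size from the article).
- Successes needed: 0.60 × 55 = 33, or 0.60 × 60 = 36.
- Progressions and progression-free deaths before 6 months of response: assumed, because the documents give neither.

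**3. Effect of the rule, 55 responders, 20 progressions, 3 progression-free deaths.**

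| Treatment of the 3 deaths | Calculation | Result | Goal |
|---|---|---|---|
| Non-events, counted as not progressed | (55 − 20)/55 = 35/55 | 63.6% | met |
| Left out | 32/(55 − 3) = 32/52 | 61.5% | met |
| Events | (55 − 20 − 3)/55 = 32/55 | 58.2% | missed |

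If the deaths are censored in a Kaplan–Meier estimate, the 6-month value lies between the first two rows, depending on when they occur. With 60 responders, 22 progressions and 3 deaths, the first and third rows become 38/60 = 63.3% (met) and 35/60 = 58.3% (missed).

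**4. How close to 60% the result must be.** With 55 responders each death recoded from non-event to event moves the result by 1/55 = 1.8 points. The number of deaths needed to turn a met goal into a missed one is (55 − progressions) − 33 + 1:

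| Progressions | Result, deaths as non-events | Deaths needed to miss |
|---|---|---|
| 22 | 60.0% | 1 |
| 20 | 63.6% | 3 |
| 18 | 67.3% | 5 |
| 16 | 70.9% | 7 |

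**5. Chance of meeting the goal.** For 55 responders this is P(X ≥ 33 | p), where p is the true proportion reaching 6 months. Counting deaths as events lowers p by the share of responders who die progression-free before 6 months (assumed 3%, 5% or 10%).

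| p with deaths ignored | Deaths ignored | 3% die | 5% die | 10% die |
|---|---|---|---|---|
| 65% | 82.1% | 67.5% | 55.8% | 27.2% |
| 70% | 95.8% | 89.3% | 82.1% | 55.8% |

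**6. The early-death sentence.** For a patient who dies before any scan:
- ORR: the first clause gives failure and the second gives failure, so they agree.
- DoR: the first clause gives failure and the second gives missing, so they conflict.
- Denominator: both statements of the DoR goal restrict it to responders. This patient is not a responder and drops out under either label.

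The conflict is therefore one of wording and has no numerical effect under the printed goal.

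**The case against.** **Detail left to the analysis plan.** Censoring rules for a time-to-event endpoint usually sit in the full protocol or SAP, which are not shown. This stands for the mechanics: the article does not say that a progression-free death is censored, excluded or counted as durable, and no one of these should be attributed to it. It does not remove the point, because the end event itself is stated, and so is a death rule that leaves out responders.

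**A deliberate choice.** The Discussion says the co-primary endpoints were chosen to measure local disease control, so a progression-only definition may be intended. Adding death does change what is estimated. That is a reason to keep the progression-only version as a sensitivity analysis. It does not say how a death that ends observation of the response should count towards a six-month durability goal.

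**Size.** Entry requires Child-Pugh A5 or A6, ECOG 0 or 1 and a life expectancy of at least 6 months, and excludes portal vein thrombosis and extrahepatic disease. Progression-free deaths soon after a response may be few. This stands: the counts above are assumptions, and a result well above 60% would survive several deaths.

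**Stronger readings that the documents do not support.**
- A reader might infer that early deaths in non-responders pull the DoR rate down by entering its denominator. The article states the goal twice in responders, so they do not.
- A reader might infer that the definition conceals treatment-related deaths. Adverse events are adjudicated by a Clinical Events Committee and summarized by outcome, grade 3 or higher toxicity is a secondary endpoint, and a DSMB reviews safety. The bias concerns the DoR estimate, not safety reporting.

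**Conclusion.** The point holds in a limited form and should be fixed. As printed, a responder's death without documented progression is not a DoR event, and this biases the co-primary proportion in the device's favour. With 55 responders the effect is 1.8 points per death. Three such deaths are enough to change the conclusion when 20 responders progress, but seven are needed when 16 progress. These figures rest on 55 to 60 responders, on assumed numbers of deaths and progressions, and on the goal being judged by the observed proportion.

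It would go too far to say that the rule will decide the trial or makes the design unsound: a change of conclusion needs a result near 60%, and the documents offer no death rate from which to judge how likely that is. The two labels for an early death are a drafting conflict that should be reconciled but should not alter the result. The ORR co-primary and its sample size are untouched.

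**What to change.** 1. For the primary analysis, define DoR in responders only, as the time from first CR or PR to the earlier of progression or death from any cause.
2. Keep progression-only DoR, as a measure of local control, as a sensitivity analysis.
3. Replace the early-death sentence with a single status: patients who die or are not evaluable before any response are ORR failures and are outside the DoR analysis.
4. If an SAP already does this, align the published definition with it. In either case fix the rule before outcome data are examined.

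The cost is one or two sentences. The DoR estimate may be slightly lower. No change to sample size, visits or data collection is needed.
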